## Abstract

**Background:**

Depression, prevalent among people living with HIV (PLWH) in Malawi, is associated with negative HIV patient outcomes and likely affects HIV medical management. Despite the high prevalence of depression, its management has not been integrated into HIV care in Malawi or most low-income countries.

**Methods:**

This study employs a pre-post design in two HIV clinics in Lilongwe, Malawi, to evaluate the effect of integrating depression management into routine HIV care on both mental health and HIV outcomes. Using a multiple baseline design, this study is examining mental health and HIV outcome data of adult (≥18 years) patients newly initiating ART who also have depression, comparing those entering care before and after the integration of depression screening and treatment into HIV care. The study is also collecting cost information to estimate the cost-effectiveness of the program in improving rates of depression remission and HIV treatment engagement and success.

**Discussion:**

We anticipate that the study will generate evidence on the effect of depression management on HIV outcomes and the feasibility of integrating depression management into existing HIV care clinics. The results of the study will inform practice and policy decisions on integration of depression management in HIV care clinics in Malawi and related settings, and will help design a next-step strategy to scale-up integration to a larger scale.

**Trial registration:**

ClinicalTrials.gov ID [NCT03555669]. Retrospectively registered on 13 June 2018.

## Background

The Joint United Nations Programme on HIV/AIDS (UNAIDS) “90–90-90” goals provide a compelling roadmap toward achieving the end of the HIV epidemic. The UNAIDS plan, which has been embraced by the international public health community and much of sub-Saharan Africa, calls for 90% of those HIV-infected to be aware of their status, 90% of those aware of their status to be on sustained antiretroviral therapy (ART), and 90% of those on ART to be virally suppressed [1]. Achievement of these goals is expected to dramatically reduce or end the HIV epidemic [1, 2]. In parts of sub-Saharan Africa (SSA), early retention in HIV care is a major obstacle to achieving the UNAIDS 90–90-90 goals. While adherence and viral suppression among those remaining in care is high [3], initiation of and retention in ART treatment (the “second 90”) has been challenging. The first year of ART treatment is a particularly vulnerable period: nearly a quarter of people initiating ART are lost to care within the first 12 months, with the majority of loss to care after the first visit or within the first few months of care [4–6].

Comorbid depression renders people living with HIV vulnerable. Comorbid depression affects patients receiving ART [7] as it is a barrier to ART retention [8, 9], associated with reduced ART adherence and viral suppression [7, 10–12].

Malawi, with a population of 17.5 million, has an adult HIV prevalence of 10% [13] and barriers reflecting challenges experienced elsewhere in sub-Saharan Africa. The Malawi Ministry of Health (MoH) has embraced the UNAIDS plans and has been a leader and innovator in expansion of antiretroviral therapy (ART) treatment programs. Yet retention in HIV care has been challenging, with only 76% of adults initiating ART being retained in care at 12 months, and only 65% being both retained in care and virally suppressed [14]. Depression is prevalent among HIV-infected adults in Malawi [15, 16] and is associated with decreased retention in care and viral suppression [7–12, 17–20]. However, Malawi has few psychiatrists and psychiatric wards to provide care [21]. The MoH is working to build capacity through task-sharing approaches, including training primary care providers and outreach workers in mental health screening and counselling [22–24].

Depression is a prime target for strategies to improved HIV outcomes in Malawi. Depression treatment has been linked to improved ART adherence in a meta-analysis comparing those receiving vs. not receiving depression treatment [25], a conclusion consistent with many observational studies [20, 26, 27], although evidence from intervention studies is mixed [28–33]. Preliminary evidence suggests that depression care may improve HIV outcomes in Africa [34–38]. In a pilot study of the integration of antidepressant management into HIV clinical care in Cameroon, in which patients with HIV and depression received treatment of amitriptyline, 87% of patients achieved full remission of their depression within 3 months [37]. Furthermore ARV adherence, viral suppression, and self-reported health also improved. Although the Cameroon study was a single-arm pilot with no comparison group, it suggests that appropriate depression care for people initiating ART may be important to achieve the 90–90-90 goals. However, more robust evidence of the impact of depression treatment on HIV care retention and treatment outcomes will be critical to help guide the allocation of resources to optimize HIV treatment outcomes.

The purpose of this paper is to present the protocol for a quasi-experimental study designed to estimate the effect of the integration of depression treatment into routine HIV primary care on both mental health and HIV-related outcomes in Malawi.

## Methods/design

### Purpose

Our evaluation study has two objectives. The primary objective of this evaluation is to assess the impact of a pragmatic, scalable mental health treatment program on HIV care outcomes including retention in care and viral suppression. The secondary objective of this study is to evaluate the impact of the mental health treatment program on mental health outcomes, including depression remission and depression response.

Specifically, our study is designed to evaluate the following hypotheses:

#### Primary

**H1** Compared to the period prior to the depression treatment program, adults with HIV and depression during the implementation of the treatment program will be more likely to be retained in HIV care and virally suppressed 6 months after ART initiation (**primary outcome**).

#### Secondary

**H2** Compared to the period prior to the depression treatment program, adults with HIV and depression during the implementation of the treatment program will be more likely to be virally suppressed 6 months after ART initiation.

**H3** Compared to the period prior to the depression treatment program, adults with HIV and depression during the implementation of the treatment program will be more likely to be retained in HIV care 6 months after ART initiation.

**H4** Compared to the period prior to the depression treatment program, adults with HIV and depression during the implementation of the treatment program will have higher HIV care appointment adherence (proportion of scheduled visits that were attended) over the first 6 months on ART.

**H5** Compared to the period prior to the depression treatment program, adults with HIV and depression during the implementation of the treatment program will be more likely to have achieved depression remission 6 months after ART initiation.

### Study design

The study employs a multiple baseline evaluation design in two clinics to evaluate the impact of the integrated depression treatment program on HIV outcomes (Fig. 1). The reasons for the choice of the study design has been described published elsewhere [39].

**Fig. 1 Fig1:**
[figure not shown]
Program implementation Phases

Study activities will last 27 months. This period includes abstracting depression screening data on patients starting ART over a 20-month period and abstracting additional treatment and outcome data for an additional 7 months to identify follow-up viral load, appointment attendance, and depressive symptom outcomes. An additional 3 months is anticipated to complete data abstraction, analyses and dissemination activities.

### Measures

We are abstracting data on HIV and mental health outcomes for patients newly initiating ART who screen positive for depression (Table 1).

**Table 1 Tab1:** Measures

	Measure	Source	Time Point
Viral Load	viral load copies/mL	Mastercard or EMR	6 month
Appointment Attendance	Appointment Dates	Mastercard or EMR	Monthly
Depressive severity	PHQ-9 Scores	Mastercard	Monthly

*EMR* Electronic Medical Record

Depressive severity is being measured using the Chichewa version (vernacular language for Malawi) of the Patient Health Questionnaire (PHQ)-9. The score of 5–9 on the PHQ-9 is considered mild depression while that of 10 and above is moderate to severe depression [40]. Providers screen all patients for depression at the time of ART initiation by administering the PHQ-9 rather than self administration because of the low literacy levels among the patients. Patients who score ≥ 5 at ART initiation are re-assessed with the PHQ-9 by the HIV provider at each subsequent ART visit. This information is captured on a form called the Mental Health Mastercard that is kept with the patient’s HIV file.

Depression Remission will be defined as a PHQ-9 score < 5 at 6 months.

Retention in HIV care will be defined as being “on time” to all scheduled ART return visits in the first 6 months on treatment. “On time” will be defined as no more than 30 days late; a secondary, tighter definition will define “on time” as no more than 14 days late At ART initiation and each subsequent ART appointment, providers give patients a follow-up appointment date and a sufficient supply of ART. This information is recorded in the patient’s chart, called an HIV Mastercard, and in the Electronic Medical Record (EMR). However, generally for the first 6 months of care, new ART patients receive a 30-day supply of ART and a return appointment date in 30 days. Most often, patients need to attend monthly ART refill appointments for their first 6 months of care in order to maintain ART supply through 6 months.

Consistent ART supply will be defined as never going more than 5 days without ART in the first 6 months, calculated from the days’ supply of ART dispensed at each appointment in the first 6 months and the time between appointments.

Viral Suppression will be defined as a viral load < 1000 copies/mL at 6 months. A viral load threshold of 1000 copies/ml was chosen as this is the threshold used in the resource-limited Malawian health care system to guide decisions about treatment failure and second-line alternatives. Viral load testing is performed at Bwaila Hospital in Lilongwe using Abbott m2000 RealTime HIV-1 assay instruments with a lower limit of detection of 40 copies/mL. The results of the viral load test are recorded in the EMR.

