### Population and sample size

We are abstracting screening data for all consenting adult (≥18 years old) patients newly initiating ART and screened for depression at the time of ART initiation at the study sites during the study period. Additional depression treatment and outcome data are being abstracted for all patients who screen positive for mild, moderate, or severe depressive symptoms (PHQ-9 total score ≥ 5) [56, 57].

We focused on two populations of interest. For the primary population of interest, all patients with depressive symptoms (PHQ-9 score ≥ 5), the original sample size was determined to provide 80% power to detect an 11 percentage point pre-post difference in the primary outcome. For the secondary (smaller) population of interest, all patients with moderate to severe depression (PHQ-9 score ≥ 10), the original sample size would provide the same power to detect an 18 percentage point pre-post difference. To achieve this power, we would require 645 patients with any depressive symptoms and 225 patients with moderate to severe depressive symptoms.

Based upon the historical rate of new ART patients (122 per month between the two clinics) and the expected prevalence of any depressive symptoms (35%) and moderate to severe depressive symptoms (12%) based on prior literature [58] [7], we originally planned for a 15-month data collection period to accrue the targeted sample. During the course of data collection, the rate of new ART patients was higher than expected but the prevalence of depressive symptoms was lower than expected. After extending the recruitment period for an additional 5 months, the accrual of new ART patients concluded with a final sample of 2084 individuals. The prevalence of mild to severe depression was 24.1% (*n* = 502) and the prevalence of moderate to severe depression was 6.3% (*n* = 131). This sample has 80% power to detect a slightly larger difference in the primary outcome of 12 percentage points (e.g. 60% vs. 72%) or a risk ratio of 1.2 for those with mild to severe depression. For those with moderate to severe depression, the sample has 80% power to detect an improvement in the primary outcome of 22 percentage points (e.g. 60% vs. 82%) or a risk ratio of 1.4.

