### Data abstraction and management

Data on viral loads, HIV appointment attendance, and depressive symptoms is abstracted from electronic and paper medical records and the depression treatment registry at the sites. ART appointment data including the date of the appointment, the expected return date, and medication prescribed is recorded in the EMR, on a paper patient file (called an HIV Mastercard), or both. The results of the viral load tests are recorded in the EMR. Data on patients’ depressive symptoms and depression treatment are only recorded on paper in an additional patient filed attached to the ART mastercard (called a mental health mastercard). The community health workers responsible for administering the Friendship Bench problem-solving therapy also maintain paper records (called a Counselling Mastercard) that capture engagement with the PST sessions. Cost information was collected using a time-audit approach to estimate costs of delivering the program, including the opportunity cost of training participation and the time providers and supervisors spend to deliver and supervise the program. Time-audit data was captured through a combination of direct observation of medical provider and counsellor encounters supplemented with self-reporting by counsellors.

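### The only defined depression outcome is a yes/no at month 6, although PHQ-9 is abstracted monthly and exists only at attended visits; keep remission for H5 but estimate it from all the scores

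*Protocol article*

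**What the plan says.** The protocol article sets out the depression outcome as follows.

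- Measures: "Depression Remission will be defined as a PHQ-9 score" below 5 at 6 months. Table 2 lists this binary variable as the only mental health outcome.
- Secondary hypotheses, H5: patients in the treatment phase "will be more likely to have achieved depression remission 6 months after ART initiation". No other hypothesis concerns depression.
- Measures, Table 1: PHQ-9 is a monthly measure. Patients scoring 5 or more at ART initiation "are re-assessed with the PHQ-9 by the HIV provider at each subsequent ART visit".
- Data abstraction and management: data on "depressive symptoms and depression treatment are only recorded on paper". No outcome interview outside the clinic visit is described.
- Purpose: the secondary objective covers mental health outcomes, "including depression remission and depression response". Response is not defined in Measures and appears in neither H1-H5 nor Table 2.
- Data analysis: coding non-retained patients as failures is stated for the primary HIV composite only. The list of secondary analyses does not mention depression.

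**The concern.** The study collects a severity score at up to monthly intervals, then defines its depression result by one threshold at one time point. This raises two issues.

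First, precision. A cut score treats a fall from 5 to 4 as success and a fall from 20 to 5 as failure, and it ignores months 1 to 5.

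Second, who has a month-6 value. The score exists only if the patient attends. The Background section says nearly a quarter of ART initiators are lost within 12 months, mostly after the first visit or in the first few months, and H3 predicts that the program changes retention. Retention as defined (no visit more than 30 days late) is not identical to having a month-6 PHQ-9, but the two are closely linked. The chance of being measured may therefore differ by phase.

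At stake is the interpretation of H5, and so of the secondary objective. The abstract also names depression remission as one of the outcomes for cost-effectiveness.

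**Working it through.** **1. The plan's own figures.** Population and sample size gives 80% power for 60% vs 72% with 502 patients and for 60% vs 82% with 131. The check assumes two-sided 5% significance and equal phases, neither of which is stated. With 251 per phase and mean proportion 0.66:

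z = [0.12 × √251 − 1.96 × √(2 × 0.66 × 0.34)] / √(0.60 × 0.40 + 0.72 × 0.28) = (1.901 − 1.313) / 0.665 = 0.885, so power is 81.2%.

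The same formula gives 79.9% for 131 patients. Both figures reproduce. They concern the primary HIV outcome; no power is stated for remission.

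**2. Baseline severity.** 502 − 131 = 371 patients scored 5-9, and 371 / 502 = 73.9%. For them, remission needs a fall of between 1 point (5 to 4) and 5 points (9 to 4).

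**3. Information kept by the cut.** For a normally distributed score cut so that a proportion p remits, the efficiency relative to comparing means is φ(z)² / [p(1 − p)], with z = Φ⁻¹(p).

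| Assumed remission | Calculation | Kept | Equivalent of 502 |
|---|---|---|---|
| 50% | 0.3989² / 0.25 | 0.637 | 320 |
| 80% | 0.2800² / 0.16 | 0.490 | 246 |
| 85% | 0.2332² / 0.1275 | 0.426 | 214 |

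The article gives no remission rate by phase and no PHQ-9 distribution, so every row is an assumption.

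**4. Absent month-6 scores: precision.** No completeness figure is given. The only retention figure for Malawi, 76%, is at 12 months and covers adults initiating ART generally. The table uses an illustrative 60% vs 72% and the formula in step 1.

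| Assumed share with a score | Patients | Power | Detectable difference from 60% |
|---|---|---|---|
| 100% | 502 | 81% | 11.8 points |
| 90% | 452 | 77% | 12.4 points |
| 76% | 382 | 70% | 13.5 points |
| 60% | 301 | 60% | 15.1 points |

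**5. Absent month-6 scores: bias.** Suppose the program has no effect on depression, with true remission of 60% in both phases. Suppose month-6 attendance in the screening phase is 85% among remitters and 65% among non-remitters, rising to 88% and 80% in the treatment phase.

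- Attenders only: 0.510 / (0.510 + 0.260) = 66.2% vs 0.528 / (0.528 + 0.320) = 62.3%, a spurious −4.0 points.
- Absentees coded as non-remitted: 0.60 × 0.85 = 51.0% vs 0.60 × 0.88 = 52.8%, a spurious +1.8 points.

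If attendance of remitters stays at 85% and that of non-remitters rises from 65% to 75%, or from 55% to 75%, the attender-only error is −3 or −7 points, and the second rule gives no error. The two simple rules can therefore err in opposite directions, and the sizes depend on the assumed attendance.

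**The case against.** The binary endpoint has a rationale in the article. Remission is the stated treatment goal of the antidepressant algorithm, and the abstract names it for cost-effectiveness. H5 is secondary, and the sample was sized on the HIV outcome. All of this stands. It is why remission should remain the H5 outcome, and why replacing it with a mean difference after accrual has closed is not recommended.

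Missing-data rules and secondary models are commonly left to a full protocol or analysis plan that is not shown. This also stands, so the lack of a rule is not itself the fault. The point is the defined outcome, which leaves the monthly scores unused.

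Three stronger readings are tempting, and the documents do not support them.

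- That H5 rests on month-6 attenders. The article fixes no analysis set for remission; absentees could be coded as failures, as in the primary composite.
- That remission is near its ceiling because 74% started at 5-9. How small a fall suffices does not show how many patients will have one. The only remission figure, 87% within 3 months, comes from a treated single-arm pilot in Cameroon and says nothing about the screening phase.
- That the cut certainly discards 36% to 57% of the information. This is 1 minus the efficiencies at 50% and 85% remission, both assumed. At high remission, scores would pile up near zero, so normality is least credible where the loss looks largest. The ratio also compares a mean shift with a proportion, which are different estimands.

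Finally, a repeated-measures model adds little for patients lost after the first visit, who have no follow-up score. That limit is real.

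**Conclusion.** The point holds in a limited form. The article defines depression success by one threshold at month 6, leaves the monthly scores out of every outcome, and measures PHQ-9 only in those who attend. The 74% figure follows directly from the article. The information kept (about 64% at 50% remission, 43% at 85%), the power loss from absent scores and the spurious differences of −7 to +1.8 points are illustrations under stated assumptions, not estimates for this study. Remission is a legitimate endpoint; the weakness is relying on the single month-6 value when earlier scores on the same patients are already being abstracted. The mention of depression response in Purpose, with no definition, hypothesis or place in Table 2, is a small inconsistency to reconcile.

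**What to change.** 1. Keep PHQ-9 below 5 at 6 months as the H5 outcome. Estimate it from a repeated-measures logistic model on all monthly follow-up scores, with phase, clinic, calendar time, month, phase by month and baseline PHQ-9. Report the adjusted month-6 remission proportions by phase and their difference. Fit the model by likelihood with patient random effects, averaging over them to obtain the proportions; an unweighted estimating-equation fit would need a stronger missing-data assumption.
2. Add the matching repeated-measures model of the PHQ-9 score as a supportive analysis, reporting the adjusted mean difference at month 6.
3. Add a sensitivity analysis for absent month-6 scores, for example with absentees coded as non-remitted, and report the number with a score by phase and month.
4. Define depression response and add it to Table 2, or remove it from Purpose.

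The cost is some extra analysis and text; no new data are needed. The models rely on scores being missing at random given the observed data. They reduce the attendance problem but do not remove it, which is why item 3 is needed.

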### Intervention program

We integrated depression screening and treatment into ART care into two clinics in Lilongwe, Malawi using a multiple baseline design in two phases: a screening phase and a treatment phase.

During the screening phase, HIV care providers screened patients for depression and monitored their depressive symptoms using the Patient Health Questionnaire-9 (PHQ-9). HIV care providers managed patients identified with depression according to existing care pathways, which included: 1) counselling by the HIV care provider; 2) referral to an on-site or off-site psychiatric nurse or other mental health specialist; or 3) in acute cases, transport to the outpatient psychiatric unit at the nearby district hospital.

At the launch of the treatment phase, HIV care providers were trained in algorithm-guided antidepressant management [38]; additionally, clinic-based lay health workers completed training in the Friendship Bench problem-solving therapy counselling protocol [38]. During this phase, providers are continuing to screen patients for depression. The providers manage cases of depression identified during the treatment phase with either antidepressants or problem-solving therapy, and providers monitor their depression treatment response at follow-up visits.

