#### Algorithm-based care for depression (ABCD)

We adapted an ABCD antidepressant prescription model. ABCD is a resource-efficient, task-sharing model for delivering high quality, effective, safe antidepressant management in non-psychiatric settings. ABCD equips non-specialists (e.g., primary care clinicians or HIV clinicians) to safely and effectively prescribe and monitor antidepressants. The model trains staff to know what to measure (e.g., depressive severity, side effects, adherence), how and when to measure it, how to interpret the results, and what resulting course of action to pursue (e.g., maintain dose, increase dose, address side effects, switch medication). Key features include (1) treatment decisions guided by regularly measured metrics of depressive severity, side effects, and adherence; (2) an algorithm summarizing best-practices care based on metrics; (3) a treatment goal of remission (full resolution of symptoms); (4) low starting dose followed by dose adjustments until remission, as long as the medication remains tolerable; (5) ensuring an adequate trial (six to eight weeks at moderate to high dose); and (6) regular structured supervision for continuous quality improvement.

In our program, a patient initiates an antidepressant when identified with moderate to severe depressive severity (PHQ-9 score ≥ 10) combined with clinical confirmation of the presence of depression (Fig. 2). Every four weeks at the monthly ART appointment, considered critical decision points (CDPs), the patient reports depressive severity and side effects using standardized measures. These metrics guide a recommendation to increase, maintain, or decrease the antidepressant dose or to change treatments. If the patient is tolerating the medication but depressive symptoms have not remitted, a dose increase is recommended. If side effects are not tolerable, the recommendation is to address them or switch treatment. At CDP3 (i.e., after 12 weeks), the patient has either achieved remission (and enters a maintenance phase) or has demonstrated treatment resistance to the current medication (and receives a new treatment plan).

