### Data analysis

The primary program evaluation question is whether the depression treatment program results in improved HIV and mental health outcomes for patients with HIV and depression relative to the standard of care prior to program implementation. The main analysis will follow an “intent-to-treat” approach, classifying patients according to screening vs. treatment phase (unexposed vs. exposed to the program) without regard to actual treatment received. In our main analysis, we will define our primary outcome, retention in HIV care with viral suppression 6 months after starting ART, as never being more than 30 days late to any scheduled return visit in the first 6 months on ART and having a viral load < 1000 copies/mL at 6 months; patients not retained or not suppressed will be coded as a failure. (Table 2**)** This composite outcome was chosen as the primary outcome because it is the definition of ART clinical success in the Malawian ART treatment system; those not retained and those retained but not suppressed are both clinical failures. This main analysis will estimate the probability of retention and viral suppression 6 months after starting ART using a generalized linear model with binomial error distribution, adjusting for calendar time and potential confounders that are imbalanced between arms at baseline, potentially including age, sex, clinic, PHQ-9 score, and presence of suicidal ideation. We will model these associations using separate generalized linear models among two samples: (a) those with mild, moderate, or severe depression (PHQ-9 ≥ 5) and (b) those with moderate to severe depression (PHQ-9 ≥ 10).

**Table 2 Tab2:** Outcome Variables

	Definition	Type
Primary Outcome		
Retention with Viral Suppression	both attending all ART appointments “on time” through 6 months and having a viral load < 1000 copies/mL at 6 months	Binary
Secondary Outcomes		
Viral Suppression	viral load < 1000 copies/mL at 6 months	Binary
Retention	attending all ART appointments “on time” through 6 months	Binary
	number of ART appointments attended through 6 months	Count
Consistent ART supply	Never going more then 5 days without ART, as calculated from pills dispensed and time between attended appointments	Binary
Depression Remission	PHQ-9 Score < 5 at 6 months	Binary

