In secondary analyses, we will consider ART care retention through 6 months (binary), number of ART appointments attended in the first 6 months (count), maintaining consistent ART supply through 6 months (binary), and viral suppression at 6 months among those retained (binary). Further, secondary analyses will take an “as treated” approach, comparing patients who receive treatment in the treatment phase to all patients during the screening phase; and an “as adequately treated” approach, comparing patients who receive adequate treatment (≥3 consecutive months of protocol-concordant antidepressant prescriptions or ≥ 4 counseling sessions) during the treatment phase to all patients during the screening phase. Data are not available on antidepressant adherence. (Table 3).

**Table 3 Tab3:** Analyses

Analysis	Definition
Primary: “intent-to-treat”	Initiated after program launch
“as treated”	Received depression treatment
“as adequately treated”	≥3 consecutive months of protocol-concordant antidepressant prescriptions or ≥ 4 counselling sessions

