### Timeline

The screening phase began at Clinic A in April 2017 and Clinic B in May 2017. The treatment phase was integrated into Clinic A after 7 months, in November 2017, and into Clinic B after 11 months, in April 2018. Identification of new patients concluded at both clinics in November 2018. Follow-up data abstraction is expected to continue through June 2019.

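### An on/off phase indicator fitted together with calendar time equals the average programme effect only if the effect is constant from launch; on this two-clinic schedule it otherwise mainly reflects the first months after launch

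*Protocol article*

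**What the plan says.** The Data analysis section describes the main analysis as "classifying patients according to screening vs. treatment phase (unexposed vs. exposed to the program) without regard to actual treatment received". Table 3 defines the exposed group as "Initiated after program launch". The primary outcome is modelled "using a generalized linear model with binomial error distribution, adjusting for calendar time"; clinic is only on a list of covariates that may be added if imbalanced. The form of calendar time and the link function are not given.

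The Timeline section fixes the schedule. Screening opened in April 2017 at Clinic A and one month later at Clinic B. On the two launches it says: "The treatment phase was integrated into Clinic A after 7 months, in November 2017, and into Clinic B after 11 months, in April 2018". Accrual ended at both sites in November 2018.

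Two statements bear on whether the effect is constant after launch. Under Intervention program: "At the launch of the treatment phase, HIV care providers were trained in algorithm-guided antidepressant management", with lay health workers trained for the counselling component at the same stage. In the ABCD section, one listed feature is "regular structured supervision for continuous quality improvement". The article describes no transition period and no term for time since launch. The as-treated and as-adequately-treated analyses change who counts as exposed but leave this time structure as it is.

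**The concern.** Within each clinic, time since launch rises one for one with calendar time. Only from November 2017 to March 2018 (five months) is one clinic treated while the other is not. From April 2018 both are treated, and Clinic A, already several months in, helps to set the time trend against which Clinic B's early treated months are judged. If the effect is still changing, that comparison subtracts part of the programme's own later effect.

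Training at launch and quality improvement under supervision make some growth plausible, and growth biases the estimate downward. The Discussion expects the results to inform national plans and a scale-up strategy. For that purpose the effect of the programme once established matters more than its effect in the first few months.

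**Working it through.** **Plan's own figure.** The article states 80% power for 60% versus 72% with n = 502. Taking 251 per phase and two-sided alpha 0.05 (both assumed): pooled SE = sqrt(2 × 0.66 × 0.34 / 251) = 0.0423; unpooled SE = sqrt((0.24 + 0.2016) / 251) = 0.0419; power = Φ((0.12 − 1.96 × 0.0423) / 0.0419) = 81%. The figure reproduces, and 12 points is used below as the full effect.

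**Inputs.** From the Timeline, with month 0 at the start of April 2017: Clinic A accrues over months 0–20 with launch at 7; Clinic B over months 1–20 with launch at 12. Assumed: uniform accrual, equal clinic volumes, risk-difference scale.

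**Formula.** Let x be the phase indicator and r its residual after regression on the intercept, calendar time and (where included) clinic. If the true effect at time s since launch is δ(s), the least-squares phase coefficient has expectation Σ r·δ(s) / Σ r, summed over treatment-phase patients. The ratios r / Σ r are weights that sum to 1.

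**Weights (linear time, clinic included).** The 29% of treatment-phase patients starting ART in months 0–2 after launch carry 0.91. The 33% starting at month 7 or later carry −0.37. The rest carry 1 − 0.91 + 0.37 = 0.46.

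**Hand check on a coarser grid.** Use 39 equal clinic-months, categorical calendar month and clinic. Exposure months 1–5 get 0.271 each, months 6–8 get 0, and months 9–13 get −0.071 each. For a ramp of 2, 4, 6, 8, 10 and then 12 points:
- Estimate: 0.271 × 30 − 5 × 0.071 × 12 = 8.13 − 4.26 = 3.9.
- True average over 21 treated clinic-months (13 in A, 8 in B): (2 × 30 + 8 × 12 + 3 × 12) / 21 = 192 / 21 = 9.1.
- Constant 12: 12 × (1.355 − 0.355) = 12.0.

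**Main results, continuous accrual, clinic included.** Ranges cover linear, quadratic, quarterly and monthly calendar time. In the window rows, staff quality ramps and each patient's effect is the mean quality over the following 6 months (equal monthly weight, assumed).

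| Effect shape, full effect 12 points | True average | Phase coefficient |
|---|---|---|
| Constant | 12.0 | 12.0 |
| Patient-level ramp, 6 months | 8.6 | 2.1 to 2.6 |
| Patient-level ramp, 13 months | 5.1 | −0.7 to −0.1 |
| Half at launch, full by month 6 | 10.3 | 7.0 to 7.3 |
| Quality ramp, 3 months, window-averaged | 11.7 | 11.0 to 11.2 |
| Quality ramp, 6 months, window-averaged | 10.9 | 8.4 to 8.8 |
| Quality ramp, 13 months, window-averaged | 7.6 | 2.6 to 3.0 |

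Without clinic in the model, the 6-month patient-level ramp gives 4.1 to 5.0 and the 13-month ramp 1.4 to 2.3. Simulated logistic models (n = 502, 60% baseline), standardised to a risk difference, give 2.3 and −0.7 for those two ramps, in line with the clinic-adjusted rows.

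**Precision.** With linear time, clinic and residual variance 0.66 × 0.34, the phase coefficient has SE 8.0 points. Adding months since launch, linear and capped at 6, and averaging over treatment-phase patients gives SE 10.4. That model recovers 8.6 for the 6-month patient-level ramp and 10.3 for the half-to-full case, but only about 2.7 of the true 5.1 for the 13-month ramp.

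**The case against.** A step exposure with calendar-time adjustment is an ordinary choice for a staggered launch and is unbiased if the effect is constant. Nothing in the article says that the effect starts at zero. The supervision phrase is one item in a general list of features of the antidepressant model, and that model is the first option only for PHQ-9 of 10 or more: 131 of 502 patients, or 26%. The other 74% receive problem-solving therapy, with a counsellor staffed at each clinic throughout. The outcome also builds up over 6 months of monthly visits, so someone starting ART on launch day still benefits from later improvement. On that view the 3- and 6-month ramps cost only 0.5 to 0.7 and 2.1 to 2.5 points, against an SE of 8.0. Much of this stands, and it is why the window-averaged rows belong beside the patient-level ones. It does not remove the mechanism: lay workers were also trained at launch, and a slow 13-month ramp still costs 4.6 to 5.0 points after window averaging.

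It can also be said that a sensitivity model belongs in an analysis plan not shown here. One may exist there. The phase coding and the calendar-time adjustment, however, are fixed in the article, and the interpretation follows from those two choices.

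Finally, the richer model is not more accurate overall. Root mean squared error for the 6-month patient-level ramp is sqrt(8.0² + 6.5²) = 10.3 for the phase model against 10.4; for the half-to-full case it is 8.6 against 10.4, and for the 13-month ramp 9.9 against 10.6. This objection stands in full and limits the remedy to a sensitivity analysis.

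**Conclusion.** The point holds as a limit on what the phase coefficient means. Unless the effect is constant from launch, the coefficient mainly reflects patients who start ART in the first months, and much, though not all, of any later change is attributed to calendar time. Growth is plausible from the text and would bias the estimate downward. For a 6-month ramp to 12 points with clinic in the model, the shortfall is about 2 points if quality is averaged over the outcome window and about 6 points if the patient-level effect itself starts at zero. Ramp length, starting level, uniform accrual and equal clinic volumes are assumptions, and leaving clinic out reduces the bias.

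A reader might infer that the estimate can be badly wrong in either direction, or that the article describes an effect that begins at nothing. The documents do not support either. Upward bias needs an effect that fades, which the text does not suggest, and near-zero or negative expected estimates arise only for a patient-level effect that starts at zero and grows over the whole 13 months, with clinic in the model.

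**What to change.** Keep the phase contrast as the main analysis. In the Data analysis section:

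- Pre-specify one sensitivity model that adds months since the clinic's launch (for example linear, capped at 6 months), with clinic and calendar time included. Report the programme effect averaged over all treatment-phase patients with its confidence interval.
- State that the phase coefficient assumes a constant effect after launch and otherwise mainly reflects the early months, so a null result alone does not show that the established programme has no effect.
- State that the sensitivity model does not override the main result.

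The cost is one extra model and two sentences; the launch dates are known and appointment dates are already abstracted. The drawback is lower precision and only partial correction if the effect drifts slowly over the whole treatment phase.
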